**Figure 2 figure2:**
[figure not shown]
The Doula Fidelity Checklist assesses adherence and competence of doulas in delivering the LHMoms sessions. LHMoms: Living Healthy for Moms; PALS: Patient-Activated Learning System.

### Screening Procedures and Eligibility Criteria

The inclusion criteria for doulas include affiliation with our community partners (CWHA or NMPP) and experience working with 10 or more clients in the catchment areas of our hospital sites. Doulas planning to move out of the area in the next year are not invited to participate.

Inclusion criteria for the RCT include birthing individuals aged 18 or older, having delivered a singleton live birth, having self-identified Black race or Latinx ethnicity, or being a Medicaid beneficiary. Exclusion criteria are birthing individuals younger than 18 years; unable to communicate in English, Spanish, or Haitian Creole; using other nonhospital doula services already; having a multifetal pregnancy, known major fetal anomaly, or stillbirth; being an active user of intravenous drugs; having known suicidal ideation with intent and plan or a known primary psychotic disorder; being on hemodialysis; having gestational age <24 weeks at delivery; and having plans to move out of the area within the next 6 months.

For the implementation evaluation cohort, doula and birthing individual criteria will be as above. For hospital staff, the only inclusion criteria will be employment at the hospital site, working on obstetrical wards, being aged 18 years or older, and being able to communicate in English, Spanish, or Haitian Creole. Staff who have no interaction with birthing parents are not invited to participate.

### Randomization and Informed Consent

At each of the 3 hospital sites, 200 participants will be enrolled and randomized, 100 per arm. The blinded study statistician creates the randomization design to randomize doulas and participants on an equal (1-to-1) basis. This study’s statistician, recruiters at each hospital, and study principal investigators remain blinded to randomization until the participant’s completion of the last study assessment, which is 6 months post hospital discharge. The randomization of participants occurs after the recruiter has obtained informed consent and completed in-hospital enrollment, before hospital discharge. The research program coordinator in the Weill Cornell Medicine Obstetrics and Gynecology Department is unblinded and executes the randomization of all RCT participants.

Doulas in both the intervention arm and attention control arm are assigned to the participants randomized to the respective arm, with no crossover, using block randomization, also designed by the blinded study statistician and executed by the unblinded research program coordinator. RCT participants are made aware of the arm to which they are randomized. Doulas and RCT participants are not blinded throughout this study, as both parties are inevitably aware of the program in which they are participating due to preparatory doula training and from session content.

After enrollment, while still hospitalized, all participants are given a home BP monitor and are taught how to take their BP using the device. All participants are asked to record BP values in a logbook provided by this study.

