### Study Population, Setting, and Recruitment

This study aims to enroll 3 types of participants for the RCT and implementation process analysis. The first is doulas, who will be trained to deliver either the LHMoms intervention or the attention control variation of standard doula care to RCT participants. The second is birthing individuals participating in the RCT. The third comprises hospital staff, including clinical providers and hospital administrators, for the implementation process analysis phase. Three hospitals in NYC that serve low-income communities will be included: the NYP Brooklyn Methodist Hospital in Brooklyn, New York; the NYP Allen Hospital in upper Manhattan, New York; and the NYC Health + Hospitals Queens Hospital in Queens, New York. These sites were chosen because they serve underresourced individuals, including high numbers of Black, Latinx, low-income, and immigrant individuals.

The selection of doulas occurred before finalization of the intervention manual, approximately 8 months before RCT participant recruitment began at our first hospital site. Doulas will be selected and trained at the other 2 sites, approximately 8 months before participant recruitment, to allow time for training and certification. There will be 8 doulas per site, with 4 being assigned to the intervention arm and 4 being assigned to the control arm, for a total of 24 doulas across all sites. Purposive sampling is used in selecting doulas, who will be recommended by our community groups based on their interests and skills.

The recruitment period for the RCT will be staggered across years 2 to 6 of this study.

There will be an 18-month recruitment period at each hospital site, and we aim to recruit 200 participants per site for a total of 600 participants. At each hospital location, a community-based recruiter will be on-site. Research staff prescreen the EHR for eligible subjects and then discuss potential recruits with onsite principal investigators and hospital staff. The care team first approaches potentially eligible patients, inquires about their interest in LHMoms*,* and informs research staff about their willingness to be contacted. Research staff then approach eligible individuals within 48 hours after their delivery and before their hospital discharge.

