## Results

Data collection for participants from each of the 3 recruitment sites will be concluded by November 30, 2027, February 29, 2028, and August 31, 2029, respectively, for Brooklyn, Queens, and upper Manhattan. Thus, after completion of follow-up study activities for upper Manhattan participants, all data for the total expected 600 participants will be collected by the end of the grant year 6, August 31, 2029. The final grant year 7, from September 1, 2029, to August 31, 2030, will be designated for completion of data analysis. Data will be analyzed on an intention-to-treat basis by study team members blinded to participant conditions.

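### The blind on the statistician, recruiters and principal investigators ends at each participant's own 6-month assessment, while sites are still recruiting, and leaves the promised blinded analysis unsecured

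*Protocol article*

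**What the plan says.** Randomization and Informed Consent in the protocol article names three roles that do not know the allocation: the study statistician, the hospital recruiters and the principal investigators. For the last two it says that "recruiters at each hospital, and study principal investigators remain blinded to randomization until the participant’s completion of the last study assessment", and the same clause governs the statistician. That assessment is the one "which is 6 months post hospital discharge". An unblinded research program coordinator carries out the allocation. On timing, "The randomization of participants occurs after the recruiter has obtained informed consent and completed in-hospital enrollment, before hospital discharge". Participants and doulas know the arm.

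Study Population, Setting, and Recruitment gives the calendar: "There will be an 18-month recruitment period at each hospital site". The target is 200 at each of the three hospitals, 600 in all. The same section says that research staff discuss potential recruits with the onsite principal investigators before patients are approached.

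The Results section, like the Abstract, promises that "Data will be analyzed on an intention-to-treat basis by study team members blinded to participant conditions". The Abstract places the start of analysis at September 1, 2029, after all data have been collected.

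**The concern.** The blind is tied to one participant's last visit, not to the end of recruitment, the last participant or database lock. Two consequences follow.

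First, the earliest participants at a site reach their 6-month assessment while that site is still enrolling. From then on the rule allows recruiters and investigators to know a growing number of past allocations. These people help decide who is approached and how the trial is presented. Staff who can link arm to participants' experience may form a view of which arm does better and let it colour those steps.

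Second, the rule has expired for everyone before the analysis begins, yet the article promises a blinded analysis. Some analytic choices in the article are open to judgement. The depression cutoff appears both as above 9 and as 9 or more, and covariates are to be picked from observed associations and baseline imbalance. An analysis plan that is not shown may settle these. Until they are settled, blinding is what keeps such choices independent of the arm results. In a trial where participants and doulas know the arm and the depression score is self-reported, staff and analyst blinding is one of the few protections left.

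**Working it through.** The protocol states no figure for this point, so there is none to reproduce. The check is timeline arithmetic.

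**Inputs from the article**
- Recruitment per site: 18 months.
- Follow-up before the blind may lapse: 6 months after discharge. Enrolment is in hospital just before discharge, so I treat the two as the same date.
- Participants: 200 per site, 3 sites, 600 in total.
- Data collection ends by November 30, 2027 (Brooklyn), February 29, 2028 (Queens) and August 31, 2029 (upper Manhattan).

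**Assumption:** even accrual, 200/18 = 11.1 participants per month per site.

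**Step 1. Overlap with recruitment.** 18 − 6 = 12 months, so in 12 of 18 recruitment months (67%) some blinds may already have lapsed. About 11.1 × 6 = 67 participants per site are enrolled before any blind can lapse, and about 11.1 × 12 = 133 afterwards.

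**Step 2. Allocations that could be known during recruitment at a site.** At month t (t > 6) the number is 11.1 × (t − 6):

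| Month | Allocations that could be known | Share of those enrolled so far |
|---|---|---|
| 9 | 33 | 33% |
| 12 | 67 | 50% |
| 15 | 100 | 60% |
| 18 | 133 | 67% |

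**Step 3. Average over all enrolments.** The month-18 figure is the maximum. The share of the site's 200 that could be known, averaged over all enrolments, is the integral of (t − 6)/18 from t = 6 to 18, divided by 18. This equals (12²/2)/(18 × 18) = 72/324 = 22%, or about 44 of 200.

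**Step 4. Sensitivity to accrual.** If the monthly rate rises linearly from zero, the share enrolled by month 12 is (12/18)² = 44%, or about 89 of 200 known at the last enrolment. If it falls linearly to zero, the share is 1 − (6/18)² = 89%, or about 178 of 200. The maximum therefore depends on the accrual pattern. The 12-month overlap does not.

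**Step 5. A role that spans sites, such as the statistician.** Upper Manhattan data collection ends by August 31, 2029, which puts its last enrolment around the end of February 2029. By then Brooklyn and Queens have finished follow-up, so the blind may have lapsed for about 200 + 200 + 133 = 533 of 600 (89%).

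**Step 6. State of the blind at analysis.** All 6-month assessments are complete by August 31, 2029. On September 1, 2029 the rule requires a blind for 0 of 600 participants, for each of the three roles. Set beside the promise of a blinded analysis, no role that the article lists as blinded is still bound to be so.

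**The case against.** The strongest reply is that the sentence says how long these roles stay blinded and describes no step at which anyone is told an allocation. That is right. A reader might infer that recruiters do learn allocations while recruiting, but the text supports only that they may.

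A reader might also infer that blinded analysis is impossible. The documents do not support that either. The analysts are unnamed members of the study team, and nothing says that the statistician is one of them. A separate analyst or masked arm codes would keep the promise. The blinding sentence could also be read as covering trial conduct and the Results statement as governing analysis. What remains is that the article does not say so, and the two statements do not fit together.

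A third tempting inference is that staff could guess the next assignment. This is weak. Randomization follows consent and enrolment, and someone else carries it out. Any known allocation is at least 6 months old, about 67 enrolments back under even accrual. Blocking is described for assigning doulas to participants already allocated to an arm, not for the participant list. The point does not rest on this.

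It is also fair to say that the rule protects each participant's own outcome assessment, that staff may form impressions anyway because participants and doulas know the arm, and that no interim analysis is described. These limit the likely size of any bias. They do not explain why the blind should end before recruitment and analysis are over.

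**Conclusion.** The point holds as a badly placed end to the blind and an internal conflict, not as demonstrated bias. The rule permits the statistician, recruiters and principal investigators to know earlier allocations in the last 12 of 18 recruitment months at each site. Under even accrual this reaches about 133 of 200 per site at the last enrolment and averages about 22% over all enrolments. The maximum is about 89 to 178 under linearly rising or falling accrual. These are counts of what may be known, not of what will be disclosed. The conflict with the promised blinded analysis needs no accrual assumption: by September 1, 2029 none of the three roles must still be blinded for any participant. All of this rests on the literal, per-participant reading. If the sponsor meant the last participant, the sentence is misworded and needs the same correction.

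**What to change.** In Randomization and Informed Consent, state that recruiters, principal investigators and the statistician stay blinded to allocation until the last participant's 6-month assessment at the last site and database lock. Add that whoever performs the primary analysis, named by role and consistently with the Abstract and Results, stays blinded until that analysis is complete, for example by working with masked arm codes.

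The cost is about two sentences. The unblinded coordinator already exists and can hold the allocation list and the key to the arm codes. Sample size, visits and data collection do not change.

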### Participant Groups

#### Intervention Arm

The LHMoms intervention arm receives the doula-delivered intervention focusing on MH and cardiovascular health. The intervention promptly begins within the first day post discharge, when the doula calls each participant to introduce herself. In the 1-7 days post discharge, LHMoms intervention participants receive daily calls and texts from their doulas. Doulas monitor participants’ BP readings, collected in a daily log, and scan for postpartum complications: infection, bleeding, stroke, hypertension, cardiomyopathy, and depression. After the first 7 days, participants begin the 12-session CBT-based intervention, delivered via phone or Zoom every 1-2 weeks (Table 1).

**Table 1 table1:** After the initial 7-day emergency detection period, the LHMoms^a^ intervention is delivered via 12 Zoom sessions^b-e^.

Session	Topic^b-d^
1	Overview, introduction to healthy thinking, and heart health
2	Sleep for mom
3	Stress
4	Bonding with baby
5	Physical activity^e^
6	Life’s Essential 8: cholesterol, BP^f^, and smoking
7	Life’s Essential 8: diabetes
8	Healthy eating
9	Relationships, community, health buddies, and asking for help
10	Planning for the future, pregnancy as a window to future health, and health passport
11	Review past session topics as desired
12	Final session and send-off

^a^LHMoms: Living Healthy for Moms.

^b^Each session includes cognitive behavioral therapy and cardiovascular health content tailored to the topic.

^c^Patient-Activated Learning System readings and videos for the next session topic are assigned for each session. Participants are also instructed to monitor their blood pressure, practice replacing negative thoughts with positive thoughts, and work on their individualized goals.

^d^Doula care is provided at each session with wellness check-ins, connections to resources, and screenings for suicidal ideation and intimate partner violence as needed.

^e^Doula care for session 5 includes a discussion of the participant’s changing body and body image.

^f^BP: blood pressure.

#### Attention Control Arm

Participants in the attention control arm receive a variation of standard doula postpartum care. Participants are instructed in the hospital on how to measure and record their BP at home daily. They do not have daily contact with their doulas in the first 7 days post discharge. Following that, they begin the 12-session attention control sessions, delivered via phone or Zoom every 1-2 weeks (Table 2).

**Table 2 table2:** Attention control sessions are delivered via 12 Zoom sessions.

Session	Topic
1	Birth experience and your body
2	Supporting mom or infant feeding support
3	Infant feeding support
4	Baby sleep
5	Human papillomavirus
6	Newborn care
7	Reproductive life cycle
8	Sudden infant death syndrome and smoking
9	Well-child care and immunizations
10	Maternal health
11	Review past session topics as desired
12	Final visit and long-term support plan

### Doula Supervision and Assessment

Intervention doulas have weekly supervision sessions with a study psychologist and the LHMoms research coordinator. These supervision sessions happen throughout the 24 months of the doulas’ participation at their respective RCT sites. These sessions help ensure that each doula is delivering the LHMoms intervention as intended. Doulas can ask this study’s psychologist or psychiatrist questions about specific participant cases, LHMoms intervention delivery, or other issues that may arise. Additionally, each month, 2 randomly sampled LHMoms sessions are audio-recorded for each doula, with the consent of the doula and participant. These sessions are evaluated using the Doula Fidelity Checklist and are evaluated by this study’s psychologist for additional factors: nonverbal and verbal communication, rapport, problem-solving, and more.

Attention control doulas also engage in weekly supervision sessions with the LHMoms study coordinator as well as leadership from the respective community organization, CWHA or NMPP, offering opportunities to ask questions about specific participant cases and other issues that may arise.

### Data Collection

Data are collected from doulas as well as participants. Doulas complete a pretrial implementation survey collecting information on their background and demographics, doula training, and their views on the NYC postpartum care landscape, as well as the feasibility and acceptability of the intervention.

For all trial participants, data are collected at baseline in the hospital predischarge, 2 weeks post discharge, 6 weeks post discharge, 3 months post discharge, and 6 months post discharge. The LHMoms study team collects data via web-based surveys on the primary outcomes of PPDS, using the Edinburgh Postnatal Depression Scale (EPDS) as a proxy for the incidence of symptoms of PPD (with scores >9 indicating the presence of PPDSs), and the “heart score,” an evaluation of LE8 provided by the AHA. Figure 3 below illustrates the key areas of LE8.

**Figure 3 figure3:**
[figure not shown]
Life’s Essential 8 includes key areas for improving and maintaining cardiovascular health as defined by the American Heart Association.

Quality of life is measured via short (15-minute) and long (30-minute) web-based surveys. Long web-based surveys, administered at baseline, 6 weeks, and 6 months, take 30 minutes to complete and assess psychosocial status and other health behaviors using the EPDS, General Anxiety Disorder Assessment, Pittsburgh Sleep Quality Index, Perceived Stress Scale, Brief Resilience Scale, Scale of Perceived Social Support, Posttraumatic Stress Disorder Checklist for *DSM-5* (*Diagnostic and Statistical Manual of Mental Disorders* [Fifth Edition]), and smoking status. Short web-based surveys, administered at 2 weeks and 3 months post discharge, take 15 minutes to complete and assess psychosocial status using EPDS, General Anxiety Disorder Assessment, and Pittsburgh Sleep Quality Index (Table 3).

**Table 3 table3:** Data are collected via short and long REDCap^a^ surveys, and in-person measurements are taken by this study’s team^b-e^.

Data collection instruments and measures	Long web-based survey, 30-min^b^	Short web-based survey, 15-min^c^	In-person measurements^d^
EPDS^e^	✓	✓	
GAD-7^f^	✓	✓	
AHA^g^ My Life Check (Heart Score)^h^	✓		
PCL-5^i^	✓		
PSS-10^j^	✓		
PSQI^k^	✓	✓	
BRS^l^	✓		
Perceived social support	✓		
Hemoglobin A_1c_^m^			✓
Cholesterol			✓
Weight and height			✓
Blood pressure			✓
Smoking status	✓		

^a^REDCap: Research Electronic Data Capture.

^b^Baseline, 6 weeks, and 6 months.

^c^2 weeks and 3 months.

^d^Baseline, 3 months, and 6 months.

^e^EPDS: Edinburgh Postnatal Depression Scale.

^f^GAD-7: General Anxiety Disorder Assessment.

^g^AHA: American Heart Association.

^h^My Life Check is only completed in baseline and 6–month-long surveys.

^i^PCL-5: Posttraumatic Stress Disorder Checklist for DSM-5 (Diagnostic and Statistical Manual of Mental Disorders [Fifth Edition]).

^j^PSS-10: Perceived Stress Scale.

^k^PSQI: Pittsburgh Sleep Quality Index.

^l^BRS: Brief Resilience Scale.

^m^Hemoglobin A_1c_: glycated hemoglobin.

In addition to web-based survey administration, study staff collect physiological data at in-person study visits. Staff perform point-of-care testing for total and high-density lipoprotein cholesterol and hemoglobin A_1c_, and measure BP, height, and weight at baseline, 3 months, and 6 months. Point-of-care testing occurs in the hospital shortly after enrollment and at a community location at 3 and 6 months for the convenience of participants.

Health care use is assessed via questions presented to all participants at 3- and 6-month post discharge regarding attendance of obstetric and primary care provider visits. This study’s team also performs an EHR review of clinical visits and encounters to understand contact with the individual health systems. A Client Satisfaction Questionnaire-8 (CSQ-8) is administered at 6 months. All data are collected in a secure REDCap database housed at the main study site. The RCT schema is shown below in Figure 4.

**Figure 4 figure4:**
[figure not shown]
The RCT schema is shown below, beginning with participant enrollment in the hospital, postdelivery, and before discharge, and continuing until 6 months post discharge. BP: blood pressure; CBT: cognitive behavioral therapy; CSQ-8: Client Satisfaction Questionnaire-8; CV: cardiovascular; FG: focus group ; HBPM: home blood pressure monitoring; KII: key informant interview; LHMoms: Living Healthy for Moms; PALS: Patient-Activated Learning System; PD: post discharge; PP: postpartum; RCT: randomized controlled trial; REDCap: Research Electronic Data Capture.

### Statistical Analysis: Analysis of the Dual Primary End Points

Preliminary statistical analysis examines baseline characteristics between study arms (LHMoms intervention vs attention control) to verify that the randomization generated comparable groups. Categorical variables are summarized as frequencies and proportions. Statistical significance is set at *P*<.05 and tested using chi-square or Fisher Exact tests for variables with low expected frequencies (eg, <5). Continuous variables are described as mean, SD, median, and IQR. Statistical significance is tested using a 2-tailed Student *t* test or Wilcoxon Rank Sum for variables with unequal variance or skewed distributions.

The primary outcome of PPDS is operationalized as the presence or absence of PPD symptoms as indexed by an EPDS score greater than or equal to 9 (EPDS >9) at 6 months post partum (Table 4). Linear mixed models, designed to account for the nonindependence of observations within the same person that is inherent to repeated measures designs, are used to estimate the mean EDPS score with 95% CIs and make group comparisons between the LHMoms intervention and attention control at baseline and 6 months post partum. This approach enables an intention-to-treat analysis whereby all participants randomized into the trial are included in the primary analysis regardless of the number of sessions completed due to the flexibility of linear mixed models to handle the presence of missing data. Baseline characteristics associated with PPDS in univariate regression models (eg, parity) or group imbalance detected at baseline are included in linear mixed models as relevant covariates.

**Table 4 table4:** Primary and secondary outcomes measured in REDCap^a^ surveys assess psychosocial status and other health behaviors, as well as health care use and patient satisfaction.

Primary or secondary	Name of outcome	Specific measure to be used
Primary	PPDS^b^	EPDS^c^≥9
Primary	Cardiovascular health	LE8^d^ (continuous measure)
Secondary	Anxiety	GAD-7^e^
Secondary	Posttraumatic stress disorder	PCL-5^f^
Secondary	Perceived stress	PSS-10^g^
Secondary	Sleep	PSQI^h^
Secondary	Resilience	BRS^i^
Secondary	Social support	Perceived Social Support Scale
Secondary	Health care use	Contact at 7 days; 6 weeks postpartum visit attendance
Secondary	Satisfaction with postpartum care	CSQ-8^j^
Secondary	Implementation process	Focus groups, surveys, and interviews

^a^REDCap: Research Electronic Data Capture.

^b^PPDS: postpartum depressive symptom.

^c^EPDS: Edinburgh Postnatal Depression Scale.

^d^LE8: Life’s Essential 8.

^e^GAD-7: General Anxiety Disorder Assessment.

^f^PCL-5: Posttraumatic Stress Disorder Checklist for DSM-5 (Diagnostic and Statistical Manual of Mental Disorders [Fifth Edition]).

^g^PSS-10: Perceived Stress Scale.

^h^PSQI: Pittsburgh Sleep Quality Index.

^i^BRS: Brief Resilience Scale.

^j^CSQ-8: Client Satisfaction Questionnaire-8.

To determine changes in the second primary outcome of cardiovascular health, we similarly compare LE8 scores from baseline to 6 months with a linear mixed model approach as previously described. Following published guidelines, the LE8 metric is summed into a 1-100 score [17,45]. In addition to comparisons of mean scores at baseline and 6 months post partum, changes in group mean scores across this period are compared (ie, the interaction between treatment and time, eg, heart health score from baseline to 6 months post partum in the intervention vs attention control participants). Components of the LE8 score include diet, physical activity, tobacco use, sleep, weight, cholesterol, blood glucose, and BP—each of the 8 elements is scored separately, and a summary score is created. An 80 or higher on the LE8 metric is considered ideal, with 50-79 being intermediate, less than 50 meaning poor, with a range of 0 (poor) to 100 (ideal). Prior work shows a 10-point change is considered clinically meaningful [46].

For both primary end points, given the longitudinal nature of the intervention, dose is an important effect for exploration. Additionally, we model a site (ie, hospital) effect as a fixed main effect and explore a site by treatment interaction (eg, given the potential for personnel [ie, doula] differences across sites, there is potential for a site-level difference in treatment response).

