### Sample Size Determination for Primary End Points

The EPDS scores from baseline to 6 months are used to analyze PPDS in LHMoms and control arms. While we considered PPDS and LE8 as dual primary end points, we chose 1 outcome to base our sample size on, which was PPDSs as defined by an EPDS score >9. This score was specifically chosen because it is used as the screening cutoff to refer for clinical evaluation in our hospital system, as it represents the possible presence of depressive or anxiety symptoms. The rate of EPDS >9 ranges from about 30% to 40% depending on other characteristics of the clinics (we selected 33.5% as the lower tertile of this observed range for our nonintervention group in the power calculation). We project we will observe a reduction in the PPDS proportion from 33.5% in the control arm to 23% in the intervention arm. This yields a minimum detectable difference of 31.5% lower incidence of PPDS in the LHMoms intervention arm compared to the attention control arm at 6 months. Our minimum detectable difference is calculated with a sample size of approximately 450 individuals (225 per study arm), assuming a 1:1 randomization, a design effect of 1.5 to account for variance among sites and doulas, a power of .90, a 2-sided significance level of 0.05, and a 20%-25% attrition. Our recruitment projection is for a sample of 600, 300 per arm; however, we have conservatively built in a 25% attrition rate for the longitudinal study (thus powering from a 450 analytic sample), although in past studies we have achieved 80%-85% retention in studies with a longer 1-year observation period [47-50].

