## Discussion

### Summary and Conclusions

This hybrid type 1 effectiveness- implementation RCT tests a novel nonspecialist intervention to prevent MH and cardiovascular health complications of childbirth. Our design is rigorous—we test the intervention against an attention control and measure numerous secondary outcomes having to do with health care use.

We hypothesize that, compared to attention control participants at 6 months post discharge, intervention arm participants will have at least 31.5% lower incidence of PPDS (score >9 on EPDS), and at least 1-point greater improvement in cardiovascular health using the LE8 score. We also expect that participants randomized to the intervention arm will experience better quality of life, reporting lower perceived stress and substance use and higher rates of resilience and perceived social support. Regarding health care use and satisfaction, we anticipate that more intervention than control individuals will have an indicated health care provider contact within the first 7 days post discharge or attend 6-week postpartum visits. We also hypothesize that intervention participants will report greater patient satisfaction with postpartum care, with higher scores on the CSQ-8 survey than control participants. We have culturally adapted an existing intervention to our local population in NYC, and will also be tracking specifics of implementation that will allow us to adapt the intervention further for other contexts. We will obtain important data from participants and key players in the implementation that will support and inform on the long-term sustainability and scalability of the LHMoms program.

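### The primary depression endpoint is defined as both EPDS ≥9 and EPDS >9, so a score of exactly 9 has no fixed classification

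*Protocol article*

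**What the plan says.** All five places are in the protocol article.

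- **Statistical Analysis: Analysis of the Dual Primary End Points.** The primary outcome is the presence or absence of symptoms, "indexed by an EPDS score greater than or equal to 9 (EPDS >9) at 6 months post partum".
- **Table 4**, the formal list of outcomes, gives EPDS ≥9 for the same endpoint.
- **Data Collection** describes the EPDS "with scores >9 indicating the presence of PPDSs".
- **Sample Size Determination for Primary End Points** bases the trial on this outcome, "which was PPDSs as defined by an EPDS score >9". It explains the cutoff as the one used for screening in the hospital system and takes the planning rates from it: "The rate of EPDS >9 ranges from about 30% to 40% depending on other characteristics of the clinics". The projection runs "from 33.5% in the control arm to 23% in the intervention arm".
- **Summary and Conclusions** in the Discussion states the hypothesis as "at least 31.5% lower incidence of PPDS (score >9 on EPDS").

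**The concern.** A binary primary endpoint needs one rule. Here one phrase contains two, and the remaining places split between them. An analyst who works from Table 4 and one who works from the sample size section would report different event counts and different rates in each arm, and could reach different conclusions from a test of proportions. Each could cite the article in support.

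The planning assumptions are attached to only one of the rules. If the analysis is run at ≥9, the 33.5% control rate and the 23% target no longer describe the endpoint being tested. Recruitment began in January 2025, so outcome data are already accruing while the rule is open.

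**Working it through.** **1. The places side by side**

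| Place | Cutoff | A score of 9 is |
|---|---|---|
| Endpoint sentence, in words | ≥9 | a case |
| Endpoint sentence, in symbols | >9 | not a case |
| Table 4 | ≥9 | a case |
| Data Collection | >9 | not a case |
| Sample size | >9 | not a case |
| Discussion hypothesis | >9 | not a case |

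The EPDS total is taken to be a whole number, so >9 is the same as ≥10. A lost character in the PDF is an unlikely cause: the endpoint sentence spells its first rule out in words, Table 4 carries the ≥ symbol, and >9 recurs in three other sections.

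**2. The plan's own figures, at >9**

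The relative reduction is (33.5 − 23)/33.5 = 31.3%; the article gives 31.5%.

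For two proportions, the number per arm is n = [z(α/2)·√(2p̄(1−p̄)) + z(β)·√(p₁(1−p₁)+p₂(1−p₂))]² / (p₁−p₂)². With p₁ = 0.335, p₂ = 0.23, p̄ = 0.2825, two-sided 0.05 and 90% power:

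n = (1.960 × 0.6367 + 1.282 × 0.6324)² / 0.105² ≈ 385 per arm before the design effect, and 578 with the design effect of 1.5.

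The stated 225 per arm is not reproduced. That is a separate matter which the cutoff does not cause. The 385 serves below only as a reference.

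**3. How many might score exactly 9 (assumption)**

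The article gives no EPDS mean, SD or distribution. Take a normal curve with P(X > 9.5) = 0.335, the continuity-corrected form of >9. The z value at 9.5 is 0.426, so at 8.5 it is 0.426 − 1/SD.

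| Assumed SD | P(≥9) | Share at exactly 9 | Increase over 33.5% |
|---|---|---|---|
| 4.5 | 0.419 | 0.084 | 25% |
| 5 | 0.411 | 0.076 | 23% |
| 5.5 | 0.403 | 0.068 | 20% |
| 6 | 0.398 | 0.063 | 19% |

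**4. A wider range**

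Because the normal shape is doubtful, let the share s at exactly 9 run from 2% to 8%.

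- Participants affected: 0.02 × 450 = 9 to 0.08 × 450 = 36.
- Projected effect for comparison: 0.105 × 225 = 23.6, about 24 events.
- Control rate under ≥9: 33.5 + s = 35.5% to 41.5%.
- If s is the same in both arms, the difference stays at 10.5 points. The relative reduction falls to 10.5/35.5 = 29.6% at 2% and 10.5/41.5 = 25.3% at 8%, and n per arm (no design effect) rises from 385 to 401 and 439.
- If the relative reduction stays at 31.3% instead, n per arm falls to 354 and 281.

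The direction of the effect on power is therefore not fixed either.

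**5. Could the result turn on it?**

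Suppose the trial observes exactly the projected rates with 225 per arm, and apply the design effect: 225/1.5 = 150 effective per arm. With z = 0.105/√(2p̄(1−p̄)/150):

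| s in both arms | Rates | z | Two-sided p |
|---|---|---|---|
| 0 (>9) | 33.5% vs 23% | 2.02 | 0.043 |
| 2% | 35.5% vs 25% | 1.98 | 0.048 |
| 4% | 37.5% vs 27% | 1.95 | 0.052 |
| 8% | 41.5% vs 31% | 1.89 | 0.059 |

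In this illustration the same data fall on either side of 0.05 according to the cutoff.

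**The case against.** Four points can be made on the other side.

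**The only model described for this endpoint is cutoff-free.** The analysis section specifies a linear mixed model on the mean EPDS score, and recoding a 9 cannot change it. This stands, and it limits the significance argument to a binary comparison. It does not remove the problem, because the endpoint, the sample size and the hypothesis are all stated as proportions.

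**The size is modelled.** The fitted normal puts 3.6% (SD 4.5) to 10.7% (SD 6) of participants below −0.5, which the scale does not allow. An SD of 3.5 would give 10.9 points at exactly 9. This also stands: the figures are illustrative, and the contradiction does not depend on them.

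**Intent is not proven.** The endpoint sentence puts >9 in brackets after the words for ≥9, so the symbol may be used loosely elsewhere, and the source rates could have been counted at either cutoff. The documents cannot exclude this, so the sponsor needs to confirm how the planning rates were counted.

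**Analysis is planned for grant year 7 by blinded staff.** Blinding makes it harder to pick the cutoff that favours an arm. It does not say which cutoff applies.

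**Conclusion.** The concern holds. The article gives two incompatible definitions of a primary endpoint, and this follows from the text alone, assuming only that a total of exactly 9 can occur. The weight of the article is on >9: the planning rates, the reason given for the cutoff and the hypothesis all use it. The endpoint wording and Table 4 say otherwise.

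The number of participants affected cannot be derived from the document. Under the normal approximation with SD 4.5 to 6 it is about 6 to 8 percentage points, which raises a 33.5% control rate to about 40% to 42%. Over an assumed 2% to 8% it is 9 to 36 of 450 participants, so the group in question may be smaller or larger than the projected effect of about 24 events. The mean-score model and the LE8 endpoint are unaffected.

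**What to change.** Write EPDS >9, with (that is, ≥10) after it, in the endpoint sentence and in Table 4, so that both agree with Data Collection, the sample size section and the hypothesis. Confirm that the 30% to 40% clinic rates were counted at that cutoff. If ≥9 is what the sponsor intends, change the other three sections, replace the 33.5% and 23% with rates counted at ≥9, and redo the sample size on them.

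Make the change by a dated amendment before anyone sees outcomes by arm, and check that the registry entry and the analysis plan carry the same cutoff. Correcting to >9 costs a few words and needs no change to data collection, since the EPDS total is recorded either way. Moving to ≥9 would also need new planning rates.
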